### Outcomes

**
*Primary- child*
**

The Pre-school Language Scales – 5
^th^ Edition (PLS 5) (
Zimmerman *et al.*, 2014) is a standardized norm referenced language assessment that yields standard scores for total language, auditory comprehension, and expressive communication. A standard score of 100 represents the performance of a typical child at a given age. Standard scores between 85 and 115 correspond to one standard deviation below and above the mean, respectively; scores within this range are considered to be within normal limits.

The Focus on the Outcomes of Communication Under Six (FOCUS-34) (
Oddson *et al.*, 2019;
Thomas-Stonell *et al.*, 2010) is a clinical tool designed to evaluate change in communicative-participation in preschool children. We have obtained a copyright license to use this tool. The parent form consists of 34 statements, aimed at taking a snapshot of children’s skills as they are on that day. Example statements include,
*my child can tell stories that make sense; my child will ask for things from other children*. Parents are asked to rate each statement using a 7 point scale, ranging from ‘not at all like my child’ to ‘exactly like my child’. This yields a total score ranging from 50 to 350 with a higher score indicating a better outcome.

**
*Secondary - child*
**

PedsQL
^TM^ (
Buck, 2012) is a standardized, parent proxy-report scale of health-related QoL in young children. The PedsQL contains 23 items and measures four health dimensions: physical, emotional, social, and school functioning (questions related to school or daycare if attended). The tool asks, “please tell us how much of a problem each item has been for your child during the past one month.” Parents are required to rate each item on a scale of 0–4 (0 indicating never a problem and 4 almost always a problem). The ratings are tallied yielding a total score for each section, the higher score indicating a greater level of difficulty.

The Child Health Utility instrument (CHU9D) (
Furber & Segal, 2015), (caregiver completed) is a generic preference- based measure, using parent report scales to measure health related quality of life, in young children. The CHU9D (for children < 5years) consists of 11 questions and parents are asked to base their responses on how their child is feeling on the day of completion. It consists of a descriptive system and a set of preference weights, which give utility values for each health state described by the descriptive system, allowing the calculation of QALYs (
Mpundu-Kaambwa *et al.*, 2017). 

**
*Secondary - parent*
**

The Maternal Responsive Behaviours Coding Scheme (MRBCS -
Levickis *et al.*, 2014) is an observational coding scheme of parent– child interaction. Implementation of the MRBCS yields a total number of occurrences for each of the four parental responsive behaviours (Expansions; Imitations; Responsive Questions; and Labels), for a given period. By summing the frequency scores for each behaviour, an overall score of parental responsiveness can be calculated. The higher the score the greater the number of parental responsive behaviours - yielding better outcomes.

**
*Secondary - setting*
**

The Classroom Assessment Scoring System (CLASS;
La Paro & Pianta, 2003) is designed to assess the quality of interactions between teachers and students in the classroom. The CLASS measures three broad domains of teacher-student interactions (Emotional Support, Classroom Organization, and Instructional Support) which are assessed across 10 specific dimensions: positive climate, negative climate, teacher sensitivity, regard for student perspectives, behavior management, productivity, instructional learning formats, concept development, quality of feedback, and language modeling. Assessors observe classrooms for a minimum period of 2 hours and assign scores on each dimension using 7-point scale.

### Recruitment

A short recruitment video will be made to explain the purpose of the study and what it entails. The clinical project manager, will meet with the local childcare committee manager; preschool managers; and school principals in each potential area, to answer any questions about the programme. Parents and early years educators will also be given information leaflets and two members of our PPI group will be involved in talking to parents and staff about the study. All preschool children enrolled in the National Childcare scheme (aged between 2 years and 8 months and 5 years and 6 months) or attending Junior Infants in the educational settings recruited for the project, their parents/caregivers, and a minimum of 1 educator at each setting, will be invited to participate in the project. It will be made explicit from the outset that all settings will not receive the intervention. Recruitment will take place over a period of two months (for each iteration). Pre/school managers/principals interested in having their educational setting participate in the project will provide verbal consent over the phone. Subsequently, they will receive a consent form via email, which will be collected by the team member responsible for conducting the research activities in the pre/school. Parents/caregivers that wish to participate in the project will be requested to return a signed consent form to the principal/manager of their school/preschool. Child participants will be recruited via their parents/caregivers.

### Data collection

Baseline assessments (all outcome measures) will be completed for children, parents, and each pre/school setting before being randomised to the experimental or control condition. Outcome measures will also be administered immediately post intervention, and at 6 months follow up. In addition, quality of life measures will also be administered at 1 year follow up. Outcome measures will be administered by the two research assistants employed on the project and 12 additional research assistants employed for the assessment periods only (all of whom will have some experience administering standardized assessments). Demographic information will be gathered from families to establish socio-economic status at the level of the child (measured through education of the primary caregiver) and if there is any history of speech and language difficulties in the family. Background information about the children will also be gathered including any diagnosed hearing difficulties, exposure to additional languages or whether they are already attending SLT. All parents taking part in the evaluation will receive a 20 euro ‘child-focused’ voucher at each assessment time point. All settings will receive a series of children’s books and control settings will receive continued professional development workshops post-intervention. Parental and educators’ intervention attendance levels will also be documented.

**
*Training*
**

Training will be given in the administration and coding of each measure as follows.

Assessors administering the
*PLS-5* will attend a training day with a senior SLT who has experience using this assessment.Assessors administering the FOCUS and the quality of life measures with parents, will be familiarised with each measure and attend a question/answer session about administration.Those administering
*The Maternal Responsive Behaviours Coding Scheme* will complete a training protocol under the guidance of the author of the coding scheme, where they will rate videos which will be compared with the ratings of the author. A criterion of 80% agreement will be required before progressing to rate the study videos.Research assistants administering or involved in reliability checking of the Classroom Assessment Scoring System (CLASS) will attend a two-day Observation Training provided by a certified CLASS trainer. Assessors will be required to code video segments online. To pass reliability they will be required to score within 1 point of the master code on 80% of all codes given, across all ten CLASS dimensions. The observation training will be given by the chief investigator who will complete the CLASS train-the-trainer programme online.

**
*Data coding and reliability*
**

Primary Outcome Measures:

PLS-5: Children’s responses will be scored live according to the instruction manual, while administering the assessment. A second research assistant blinded to the participants’ group allocation, will independently examine 20% of randomly selected assessments to determine the reliability of the online scoring (checking total raw score accuracy and conversion to standard scores). Point-to-point agreement will be calculated between scorers.FOCUS ©- Will be completed over the phone with parents. The research assistants will document parent responses. 20% of the forms will be randomly selected for rescoring.

Secondary Outcome Measures:

Child: QoL measures will be administered by phone and scored ‘live’ by the RAs during each phone interview. 20% of the forms will be randomly selected for rescoring.Parent: The MRBCS videos will be rated by an RA trained in the use of this measure, who is blind to time and group. 20% of the videos will be randomly selected for double coding by another RA, again blind to time and group.Pre/school: Trained testers will administer the CLASS independently ‘live’ in each pre/school (designated as primary observers). 20% of the settings will be randomly selected to be rated by an additional observer and reliability will be reported.

### Data management

Quantitative variable measurements will be recorded in international standardized units. Variables will be recorded within Comma Separated Value (.csv) data tables and range checks will be conducted for data values. Data files will include meta-data identifying title, creator, keywords etc. in line with the Dublin Core Metadata Initiative. Accompanying data dictionaries will be developed in parallel. The Electronic Data Capture platform (Castor EDC) will be used throughout this project. The Castor EDC platform contains in-built audit trail supports and data validation processes aligned to enact FAIR data outputs. Qualitative data will be imported into an NVivo database to facilitate analysis. Data will be encrypted at rest and in transit, two-factor authentication at log in, and daily backup and file syncing. All data will be stored so that it is amenable to audit. The PI ([name]) is responsible for data governance and the research team are working closely with the university data steward to create a comprehensive data management plan.

RAs will digitise parents’ responses into Castor at collection

### Statistical considerations

**
*Planned sample size*
**

The trial is designed to have reasonable power to detect a modest intervention effect. Using
*a priori* power calculations based on the goal of detecting an effect size of Cohen’s d = 0.25, with a power of 80%, an intra class correlation of .05 (with an average of 10 participants per cluster) and a standard significance level of 5%, the required number of clusters is 72. We targeted a modest effect size based partly on the 1) the pilot trial of Happy Talk (
Frizelle *et al.*, 2021b), which showed standardized effect sizes of 0.6 SD (
*p* = 0.005), 0.21 SD (
*p* = 0.26) and 0.46 SD (
*p* = 0.01) for receptive, expressive and total language scores, respectively; 2) the empirical literature which shows an effect of d = 0.3 for expressive language (
Heidlage *et al.*, 2020); and 3) research showing that intervention effects are often reduced when implemented at scale (
Bleses *et al.*, 2021). Further, the sample size calculations are conservative in that they do not account for efficacy gains following from stratified randomization; subsequent statistical adjustment for said stratifiers; and additional, prognostic participant- and cluster-level covariates in analyses of the trial data. Finally, we will include an additional 2 participants per cluster to allow for loss to follow-up, based on retention figures from our pilot trial, resulting in a target of 864 total participants enrolled in the trial.

**
*Randomisation, allocation concealment and blinding*
**

At the start of each of the two study cycles, 36 of 72 settings will be randomly allocated to either the Happy Talk or the “business as usual” study arms following their enrolment. The randomization will be stratified by geographical region and preschool versus school and restricted within strata using a block size of 2. Then, from the consenting families within each setting, 12 children and their parents/ caregivers will be randomly chosen at the start of the school year for assessment of study outcomes. The randomization lists for both settings and children/families will be prepared under the Standard Operating Procedures of the HRB-CRF-UCC. Allocation concealment will be maintained through the use of a protected electronic database so that the allocation will only become available to interventionists, when pre/schools and their associated families have unambiguously consented and enrolled onto the trial and when baseline measures have been completed. The study will then be open label from that point, as both participants and study staff delivering the interventions will be aware of how settings were allocated. However, outcome assessors will remain blind to allocation, and the initial analyses of the study data will be done by a blinded study statistician.

**
*Data analysis*
**

Analyses of study outcomes will be done at the participant level, and not based on cluster level summaries of participant data. Further, while we don’t expect cross-over between study arms, all participants will be analysed as members of the arm they were randomized to. Further, given the pragmatic focus on the trial, participants’ data will be analysed without consideration for their degree of engagement, or lack thereof, with the study interventions (using an intention to treat analysis). Supplementary analysis will examine the impact of high versus low engagement across parents and educational settings.

Given the Happy Talk design, between arm differences in the primary child language outcomes (PLS-5, FOCUS 34) measured immediately post-intervention and 6 months later will be estimated using linear mixed effects models for repeat measures (
Bell & Rabe, 2020) with a random effect for setting, and fixed effects for study arm, timepoint, baseline outcome scores, study cycle, and geographic region (following from the stratified randomization). We will also use a second set of similar models that further adjust for setting type and gender mix, and child age, primary caregiver education, family history of speech and language difficulties, diagnosed hearing difficulties, exposure to additional languages, and any current or previous SLT. Our estimates of between arm differences in timepoint specific outcomes will be reported alongside 95% frequentist confidence intervals without consideration for multiple comparisons (
Althouse, 2016). Missing data will be carefully evaluated and a plan for addressing them will be based on what we observe. However, our planned mixed effects models for repeat measures will produce unbiased estimates assuming data are missing at random (
Bell & Rabe, 2020), conditional on model covariates. Analyses for secondary outcomes will follow a similar strategy using generalized mixed effects models for repeat measurements, using a link function appropriate for each outcome.

All analyses will be conducted under the quality system of the HRB CRF-UCC. A statistical analysis plan is available on the Open Science Framework (
https://osf.io/ns7u5/). Any necessary deviations from this SAP will be documented and explained in the trial report. All reporting will carried out in accordance with CONSORT guidelines for clinical trials.

**
*Data monitoring*
**

As this is a low risk trial (of a complex intervention), the Steering Committee will also act as the Independent Data Monitoring Committee (IDMC). They will monitor the safety of participants and make recommendations to the management group in relation to ethical issues and maintaining the integrity of the trial. To ensure protocols in relation to governance and safety monitoring are strictly adhered to, the steering committee includes personnel who can monitor and give expert advice that is completely independent of the PI; the trial managers; the research team members; and the institutions involved. More details regarding steering committee membership are provided in the supplemental material.

Because data collection will take place over two cycles, we will have an opportunity to conduct an interim analysis at the end of the data collection completed for the first cycle. At this stage, we will know if the cycle 1 recruitment targets were met, and also be able to estimate the degree of clustering and variance we observed for the outcomes. This information will in turn facilitate a sample size re-evaluation that can inform how the study proceeds for the second cycle. If the re-analysis suggests that an increased sample size target is required for cycle two, this will be carefully considered by the Trial Steering Committee (if no such increase is suggested, then the study will proceed as planned). At this stage, the Trial Steering Committee will have the option of requesting a formal futility analysis to help determine whether the trial should continue or be stopped prior to data collection in year two. Details of the analysis and the results of the Trial Steering Committees’ deliberations will be reported back to the funder and a final decision will be negotiated by all stakeholders.

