**Method:**

The Happy Talk trial is a large scale cluster randomised trial of a 12-week manualised intervention delivered in pre/school settings serving socially disadvantaged communities, in Ireland. Seventy-two clusters will receive the intervention (12 participants per cluster). Parents and pre/school staff engage in group training and coaching in the form of 12 1-hour sessions for parents and four staff workshops, over the course of the pre/school year. Training/coaching includes core interaction skills (modelling, expanding, balancing questions and comments), early literacy and phonological awareness. Blinded assessments pre- and immediately post-intervention and at 6 months follow up, will measure the primary outcomes of children’s receptive and expressive language and functional impact, and secondary outcomes of quality of life. Parental responsiveness and educator-child interactions will also be evaluated.

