1.Children in the intervention group will have better mean scores ona.Receptive, expressive and total language score on the standardized language measure, the Preschool Language Scales (PLS-5)b.Focus on the Outcomes of Communication under Six (FOCUS)c.Paediatric Quality of Life Inventory (PedsQL) and Parent report for Toddlers and Child Health Utility instrument (CHU9D), we have delayed follow up measures to 1 year post to allow time for programme effects to translate into QoL impact.2.Parents in the intervention group will have higher mean scores on the Maternal Responsive Behaviours Coding Scheme (MRBCS)3.Early childhood education settings in the intervention group will have higher means scores on the Classroom Assessment Scoring System (CLASS)4.The intervention will be cost effective for the health care system (measured against common decision thresholds).

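### FOCUS-34 and the quality-of-life scales are described as blinded but are rated by parents who know their allocation, and a sample size for one comparison is tied to no named primary score or timepoint

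*Protocol article*

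**What the plan says.** **Blinding.** The abstract (Method) states: "Blinded assessments pre- and immediately post-intervention and at 6 months follow up, will measure the primary outcomes". It lists functional impact among those primary outcomes and quality of life as secondary. Under Randomisation, allocation concealment and blinding, the protocol says the trial is open label once allocation is released and that "both participants and study staff delivering the interventions will be aware of how settings were allocated", while those who assess outcomes stay blind. Under Outcomes, FOCUS-34 is a set of statements that parents score on a 7-point scale, and PedsQL and CHU9D are also parent or caregiver reports. Under Data coding and reliability, FOCUS "Will be completed over the phone with parents", with research assistants writing down the answers. The quality-of-life scales are also taken by telephone. MRBCS is coded from video by a rater blind to time and group. CLASS is observed live in the setting. In the intervention arm, parents are offered twelve one-hour training and coaching sessions (Interventions).

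**Primary comparisons.** Outcomes lists PLS-5 and FOCUS-34 as primary for the child. The hypotheses name "Receptive, expressive and total language score on the standardized language measure" and then FOCUS. Data analysis plans to estimate "between arm differences in the primary child language outcomes (PLS-5, FOCUS 34) measured immediately post-intervention and 6 months later", with timepoint-specific 95% intervals reported "without consideration for multiple comparisons". Planned sample size rests on a single effect of 0.25 SD; the ICC is 0.05, ten children are analysed in each cluster, and the target power is 80%. The conclusion drawn there reads: "a standard significance level of 5%, the required number of clusters is 72".

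**The concern.** For a parent-reported scale the parent is the assessor. The research assistant on the telephone may be blind, but the judgement being recorded comes from someone who knows which arm the setting is in and who, in the intervention arm, may have given many hours to the programme. A reader of the abstract would credit FOCUS-34 and the quality-of-life scales with a protection against expectation that only the directly assessed and observer-coded measures can have.

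The second issue adds to the first. Several scores at two timepoints are primary, none is named as deciding, and the sample size supports one comparison. The article therefore does not rule out a headline claim of benefit that rests on the unblinded primary outcome alone.

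**Working it through.** **1. Who makes the rating, and do they know the allocation?**

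| Measure | Source of the score | Aware of allocation after baseline? |
|---|---|---|
| PLS-5 | child tested directly, scored by research assistant | no, by the general statement on assessors |
| MRBCS | coded from video | no, stated explicitly |
| CLASS | live observer in the setting | no, if the general statement on assessors is kept for these observers |
| FOCUS-34 | parent, by telephone | yes |
| PedsQL, CHU9D | parent, by telephone | yes |

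Baseline is collected before randomisation, so baseline parent ratings are unaffected. The abstract's description fails for the last two rows after baseline.

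**2. The plan's own sample size.** Inputs from Planned sample size: d = 0.25 (SD 1), power 80%, 5% significance (taken as two-sided), ICC 0.05, 10 analysed per cluster. Equal allocation is assumed.

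- Per arm without clustering: 2(1.960 + 0.842)²/0.25² = 251.2, or 252 rounded up.
- Design effect: 1 + (10 − 1) × 0.05 = 1.45.
- Clusters: 2 × 251.2 × 1.45/10 = 72.8, against 72 stated.
- Power at 72 clusters: effective n per arm is 360/1.45 = 248.3 and the standard error is √(2/248.3) = 0.0898, giving 79.5% (78.4% with a t reference on 70 df).

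The stated figure is reproduced as a two-sided 5% test of **one** comparison. A one-sided 5% test would need only about 57 clusters.

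**3. Size of a possible expectation effect on FOCUS-34.** The documents give no figure, so these shifts are illustrative. With no true effect and the same design inputs, a rating shift b favours the intervention with probability Φ(b/0.0898 − 1.96):

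- b = 0.10 SD: 20%
- b = 0.20 SD: 61%
- b = 0.25 SD: 80%

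**4. How many primary contrasts?**

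- Four, if Data analysis means two instruments at two timepoints.
- Six, from the abstract (receptive, expressive and functional impact, at two timepoints).
- Eight, from the hypotheses (receptive, expressive, total and FOCUS, at two timepoints).

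**5. Error if any one interval were enough.** For independent contrasts the two-sided chance is 1 − 0.95^k: 18.5%, 26.5% and 33.7% for k = 4, 6 and 8. In the benefit direction it is 1 − 0.975^k: 9.6%, 14.1% and 18.3%. The scores are not independent, so these are too high. The documents give no correlations. A multivariate-normal simulation (500,000 draws, PLS-5 total taken as the sum of the two subscales) under assumed values gives:

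| Receptive–expressive / PLS–FOCUS / between timepoints | 8 contrasts: two-sided, benefit | 4 contrasts: two-sided, benefit |
|---|---|---|
| 0.5 / 0.2 / 0.5 | 24%, 12% | 17%, 9% |
| 0.7 / 0.3 / 0.6 | 22%, 11% | 16%, 8% |
| 0.7 / 0.4 / 0.7 | 20%, 10% | 15%, 8% |
| 0.8 / 0.5 / 0.8 | 18%, 9% | 14%, 7% |

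For a false claim of benefit the relevant range is 7-12%, against 2.5% for one contrast.

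**6. Cost of adjusting instead (Bonferroni, same inputs).** Two contrasts need about 90 clusters (power at 72: 70.7%), four need 104 (61.3%), and eight need 120 (52.0%).

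**The case against.** The methods text is open about the design. It says the trial is open label after allocation, that participants know their arm, and that parents supply the ratings by telephone. On that view the fault is a broad phrase in an abstract. This stands in part: nothing is hidden, and baseline ratings are unaffected. But the general statement that outcome assessors stay blind makes no exception for parent reports either, so the correction is needed in both places.

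A reader might infer that intervention parents are coached on the very items they rate. The documents do not support this. FOCUS-34 rates the child's communication, while the sessions largely teach adult techniques meant to promote it. Awareness and investment are enough for the concern.

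On multiplicity, reporting estimates with unadjusted intervals is a deliberate choice with a citation, and a decision hierarchy may sit in the statistical analysis plan, which was not available here. Both points stand. A reader might also infer that eight tests are each made at 5% and that any one makes the trial positive. The protocol says neither. The 5% level appears only in the power calculation, eight is the highest of three readings, and no success rule is stated. If all contrasts had to succeed, there would be no inflation but power would fall.

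Finally, long-term impact and functional outcomes are stated aims, so giving FOCUS-34 or the 6-month visit less weight is a trade-off and not a correction of an error.

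**Conclusion.** The blinding description is wrong as written for FOCUS-34, PedsQL and CHU9D after baseline. This rests on the text alone. How large the resulting bias would be is unknown; the 20% and 61% figures only show that a modest shift would matter at this sample size.

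The multiplicity point holds in a limited form. Four to eight contrasts are primary, none is named as deciding, and the 72 clusters correspond to one comparison. The 7-12% risk of a false benefit claim (14-24% two-sided) applies only if a single favourable interval were treated as sufficient, and it depends on assumed correlations. The independent-test figure of 33.7% overstates the risk, because the scores are correlated and it counts intervals favouring control.

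**What to change.** 1. In the abstract and in the blinding section, limit the word blinded to PLS-5, MRBCS and, as far as its observers are kept blind, CLASS. Describe FOCUS-34, PedsQL and CHU9D after baseline as unblinded parent reports.
2. State that a difference on these parent reports alone does not establish effectiveness.
3. Tie the sample-size statement to one named, blind-assessed PLS-5 score at one timepoint, matching any rule already in the statistical analysis plan. This keeps 72 clusters at about 80% power. Report the other contrasts as supporting estimates with unadjusted intervals, as now planned.
4. Name the model for that comparison explicitly. The first model set adjusts for cycle and region, but setting type, also a stratification factor, enters only in the second set. A phrase such as adjusted for the stratifiers would therefore be ambiguous.

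The cost is that FOCUS-34 carries less weight as headline evidence, and that the change must go through the amendment route described under Ethics and consent. No extra clusters or data are needed.

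### The first-listed mixed models for PLS-5 and FOCUS-34 adjust for region as a stratifier but leave out preschool versus school, the other stratification factor

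*Protocol article*

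**What the plan says.** All three statements are in the Protocol article under Statistical considerations.

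- Randomisation, allocation concealment and blinding: "The randomization will be stratified by geographical region and preschool versus school and restricted within strata using a block size of 2".
- Data analysis, first set of models for the primary child language outcomes: a random effect for setting, and "fixed effects for study arm, timepoint, baseline outcome scores, study cycle, and geographic region (following from the stratified randomization"). Preschool versus school is not in this list. A further sentence adds: "We will also use a second set of similar models that further adjust for setting type and gender mix, and child age", followed by caregiver education, family history, hearing, other languages and therapy history.
- Planned sample size: the calculations are called conservative because "they do not account for efficacy gains following from stratified randomization; subsequent statistical adjustment for said stratifiers", and also take no credit for prognostic covariates.

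The article calls the outcomes primary. It does not call either set of models primary.

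**The concern.** The article gives the stratified randomisation as its reason for including region, then leaves out the other factor used in that randomisation. Stratifying by setting type balances it between arms, so differences between preschools and schools add almost nothing to the true sampling error of the treatment effect. A model without the factor still counts those differences as between-setting variance, in the random effect for setting. Its standard error then exceeds the true sampling error.

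At stake are precision and clarity, not validity. The first set may report wider intervals than the design earned. No model adjusts for the design factors alone, because setting type arrives only with a long list of other covariates. Each outcome also has two estimates and no stated choice between them.

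A residual difference by setting type is plausible. Ages run from 2;10 to 5;11, FOCUS-34 is described as a total of parent ratings with no mention of age norms, and usual care differs between the preschool programme and the Junior Infant curriculum.

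**Working it through.** **Inputs.** From Planned sample size: d = 0.25, power 80%, ICC 0.05, 10 analysed children per cluster, 5% significance level, 72 clusters. Assumed: a two-sided test, 36 settings per arm (from blocks of 2), total SD 1, and 0.05 as the between-setting variance including any part due to setting type.

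**1. The plan's own figure.** An individually randomised comparison needs 252 children per arm. The design effect is 1 + (10 − 1) × 0.05 = 1.45. Then 252 × 1.45 = 365.4 per arm, or 36.5 clusters per arm and 73.1 in total, against 72 stated. With 36 per arm, power is 79.5% (normal) or 78.4% (t, 70 df). Enrolment is 72 × 12 = 864. The stated size therefore reproduces closely, and the disputed term does not enter it.

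**2. Variance of a setting mean.** v = 0.05 + 0.95/10 = 0.145. The model without setting type reports SE = √(2 × 0.145/36) = 0.0898.

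**3. Effect of the omission.** Let setting type explain a share s of the 0.05. Because it is balanced by design, the true variance of a setting mean for the comparison is v′ = 0.145 − 0.05s. Excess interval width is √(v/v′) − 1. With an equal split of types, share s corresponds to a preschool–school difference of 2√(0.05s) SD after baseline adjustment.

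Power without the term is Φ((0.25 − 1.96 × 0.0898)/SE′), and with it Φ(0.25/SE′ − 1.96), where SE′ = √(2v′/36).

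**4. Simulation check.** 72 settings in 8 region groups of 9, two types, blocks of 2 within region by type, linear model on setting means with region indicators, 5,000 trials per case. The coverage column and the second power figure in each pair come from this, with an equal split of types.

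| Share s | Difference (SD) | v′ | Excess width | Coverage without term | Power without (formula / simulated) | Power with (formula / simulated) |
|---|---|---|---|---|---|---|
| 0% | 0 | 0.145 | 0% | 94.7% | 80% / 78% | 80% / 78% |
| 25% | 0.22 | 0.1325 | 4.6% | 95.5% | 81% / 79% | 83% / 81% |
| 50% | 0.32 | 0.120 | 9.9% | 96.3% | 82% / 79% | 86% / 85% |
| 100% (extreme) | 0.45 | 0.095 | 23.5% | 98.1% | 85% / 81% | 93% / 92% |

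A 25:75 split of types gives similar results. If total variance is held at 1 after the setting-type part is removed, the design effect falls from 1.45 to 1 + 9 × 0.0375 = 1.3375 or 1 + 9 × 0.025 = 1.225. Excess width is then √(1.45/1.3375) − 1 = 4.1% and √(1.45/1.225) − 1 = 8.8%. Hence the ranges of about 4–5% and 9–10%.

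**The case against.** The strongest reply has four parts.

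- **The adjustment is planned.** The second set includes setting type, read here as the preschool/school factor. The sample-size sentence on "subsequent statistical adjustment for said stratifiers" goes on to prognostic covariates, most of which appear only in that second set. It is fairly read as describing the analyses as a whole, not a promise about every model. This stands: a reader might infer that adjustment for the stratifiers is absent from the trial, and the article does not support that. What remains is that the first set gives stratification as its reason and then carries only one of the two factors.
- **The loss may be nil.** Baseline score is in every model and PLS-5 standard scores are age-referenced, so little may be left for setting type to explain. This stands. A reader might infer that the intervals are certainly too wide, but that depends on a difference the article does not report.
- **Planned power is not harmed.** The sample size takes no credit for adjusting for stratifiers, and power without the term stays near 80% throughout the table. This stands. The loss is a gain forgone.
- **The analysis plan is separate and not shown.** It may name the primary model and its covariates. That does not repair an explicit list in the article that does not match the article's own randomisation.

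A reader might also argue that the study cycle term is redundant because each healthcare area belongs to one cycle. The article never defines geographic region as healthcare area, so this does not follow.

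**Conclusion.** The mismatch holds: region is in the first set because of the stratification, preschool versus school is not, and neither set is named as primary. The consequence is conditional and in the safe direction. The treatment estimate is unbiased, and the reported standard error is too large only as far as setting type predicts outcome beyond baseline score. Under the plan's ICC and cluster size, a 25% share costs 2–3 points of power and a 50% share about 5. A share of zero costs nothing and cannot be excluded, especially for PLS-5. Calling the first set the primary analysis would be an inference, since the article gives neither set that label. The 72 clusters, 864 participants and 80% power are unaffected.

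**What to change.** Add preschool/school as a fixed effect in the first set of models for PLS-5 and FOCUS-34, or replace region with the region-by-type stratum. State that this set is primary, and keep the second set for the remaining prognostic covariates. Settle this before any unblinded analysis. If the separate analysis plan already says so, correct the article's list to agree.

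The cost is one sentence of text and one degree of freedom for the single term (more for the stratum version). The factor is needed to randomise, so it is known for every setting and requires no new data. If it explains nothing, the simulation shows no material loss from including it (power 78% with or without).
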